## Discussion

Individuals with ABI have difficulties in integrating and maintaining an active lifestyle after rehabilitation discharge. In line with this, they have expressed a need for long-term (after)care close to home, including guidance on an active lifestyle. This study addresses these aspects by implementing the ABI-MOTION intervention using a network of rehabilitation and community-based services. The hybrid implementation study design provides insight into both the implementation process and intervention effects. This helps to understand which aspects of the intervention work and are feasible in practice.

### Potential benefits

We expect that, after the implementation of the ABI-MOTION intervention, more patients will be guided to an active lifestyle after rehabilitation discharge. If they succeed in adopting and sustaining an active lifestyle, patients may directly benefit from the ABI-MOTION intervention. In addition, since the ABI-MOTION intervention addresses the specific needs of individuals with ABI with regard to the aftercare phase, we expect that their HR-QoL may improve.

### Limitations

This protocol has several limitations. First, as this is a hybrid implementation study with a primary focus on implementation outcomes, the pre–post effect evaluation is considered secondary. Consequently, findings should be interpreted as exploratory. In addition, the involvement of researchers in participant recruitment for the effect evaluation limits the ability to fully observe the course of the implementation process and may influence implementation outcomes. Furthermore, the relatively small sample size limits the number of covariates that can be included in the effect evaluation analyses and may reduce the precision of the estimated effect. Finally, as the study is conducted within a specific regional network in the Netherlands, the generalisability of the findings to other settings or healthcare systems may be limited.

### Ethics, safety and dissemination

This study has been approved by the Medical Ethics Committee of Erasmus MC (MEC-2023-0623). Participation is voluntary and participants can withdraw their consent at any time. This will have no impact on their treatment. The rehabilitation physician examines contraindications for moderate to vigorous exercise in a physical examination, which is standard practice during outpatient rehabilitation. Suffering from contraindications for performing moderate to vigorous exercise and activities is not an exclusion criterion for the study. Instead, the contraindication and specific advice on how to exercise safely will be discussed with the sports consultant. Harms are defined as any adverse events or unintended negative consequences potentially related to study participation. Given the low-risk implementation design, harms will be assessed non-systematically through reporting by the researchers.

The handling of personal data complies with the European Union General Data Protection Regulation and the Dutch Act on Implementation of the General Data Protection Regulation. All data is coded before storing and is therefore not retraceable to the individual patient. The key to the code will be safeguarded by the investigator. Individual de-identified participant data and statistical code will be available after study completion on reasonable request.

The procedures in this study will continuously be monitored by the members of the research team, especially by the investigator. Also, a qualified independent monitor is appointed, who is not a part of the research team. The database will be monitored every 3 months for completeness and accuracy of the data registration. A random check will be performed every quarter of a year on the completeness and accuracy of the data of at least 10 patients. If any, all protocol amendments will be notified to the Medical Ethics Committee of Erasmus MC

The sponsor/investigator has a liability insurance which is in accordance with the legal requirements in the Netherlands (Article 7 Wet medisch-wetenschappelijk onderzoek met mensen). This insurance provides cover for damage to research subjects through injury or death caused by the study. The insurance applies to the damage that becomes apparent during the study or within 4 years after the end of the study.

The results of the study will be disseminated in peer-reviewed journals, conferences and in stakeholder meetings.

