### ABI-MOTION intervention

The ABI-MOTION intervention consists of 5 activities (figure 1). The programme starts with outpatient rehabilitation for patients with ABI (1), provided in the rehabilitation centre by a multidisciplinary team which may include a rehabilitation physician, physical therapist, occupational therapist, psychologist and/or movement therapist. In addition, during outpatient rehabilitation a brain education flyer is provided by a physical therapist (2), with information about ABI, PB guidelines and benefits of an active lifestyle. The community-based service will be integrated in outpatient rehabilitation by arranging an introduction of the participant to a sports consultant during outpatient rehabilitation (3). After rehabilitation discharge, patients may receive a maximum of 8 hours of sports consultancy, depending on their needs, which is delivered by the sports consultants of the SportMEE programme (4). There are no eligibility criteria for the SportMEE consultancy programme. About 6 and 12 months after rehabilitation discharge, the patient has follow-up consultations with the rehabilitation physician (5) as part of outpatient rehabilitation care. The control group receives activities 1 and 5. The intervention group receives all 5 activities.

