For the explorative effect evaluation, participants are followed up to 1 year after discharge from outpatient rehabilitation and will undergo four measurements; a baseline measurement within the last 4 weeks of outpatient rehabilitation and before the start of the other parts of the ABI-MOTION intervention (T0), and at 3 (T1), 6 (T2) and 12 (T3) months post-rehabilitation discharge. Measurements include physical and cognitive functioning tests at the rehabilitation centre, home measurements including activity monitoring and an electronic diary, and (online) self-report questionnaires sent to the participants by mail or postal mail. The T1 measurement consists of (online) self-report questionnaires only. The T0 measurement aligns with an outpatient rehabilitation visit, and T2 and T3 with standard care follow-up visits at the rehabilitation physician (figure 1). During the visits at the rehabilitation centre (T0, T2 and T3), a trained research assistant conducts the tests, asks general questions and provides information and requirements for the home measurements. To reduce potential burden, participants are given flexibility to complete the questionnaires at their own pace, including the option to pause and resume at a later time. Since implementation outcomes are the primary focus, participants who are unable to complete the questionnaires independently (eg, due to aphasia) are not required to do so. Support of proxies in completing the questionnaires is allowed; however, proxies are asked not to complete the questionnaires on behalf of participants.

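### Harms are collected non-systematically and only if judged related to participation, so they are likely to be under-counted and may be captured differently in the two groups

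*Protocol article*

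**What the plan says.** All of the harms plan is in the protocol article under Ethics, safety and dissemination.

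- **Definition.** "Harms are defined as any adverse events or unintended negative consequences potentially related to study participation".
- **Method and reason.** "Given the low-risk implementation design, harms will be assessed non-systematically through reporting by the researchers".
- **Who may enrol.** "Suffering from contraindications for performing moderate to vigorous exercise and activities is not an exclusion criterion for the study".
- **Safeguard.** The rehabilitation physician examines contraindications as part of usual outpatient care. The next step reads: "Instead, the contraindication and specific advice on how to exercise safely will be discussed with the sports consultant".

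Two other sections bear on the point.

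- **Contacts by group** (ABI-MOTION intervention). "The control group receives activities 1 and 5. The intervention group receives all 5 activities". The additional activities are the education flyer, the introduction to a sports consultant and the consultancy, of which "patients may receive a maximum of 8 hours of sports consultancy" after discharge.
- **Research contacts** (Data collection). "During the visits at the rehabilitation centre (T0, T2 and T3), a trained research assistant conducts the tests, asks general questions". Between baseline and 6 months there is one further contact: "The T1 measurement consists of (online) self-report questionnaires only". No difference between the groups is stated for this schedule.

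**The concern.** The article fixes a method and gives a reason for it, so this is not detail left to a fuller document. The reason is low risk. It sits uneasily beside enrolment of people with exercise contraindications in a programme that guides participants towards sport and exercise in the community. Falls, injuries and new cardiac or neurological events would mostly happen at home or at a sports location. Under the plan they enter the harms record only if a researcher comes to hear of them and considers them potentially related to participation.

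The intervention is to be adjusted while the study runs, and a plan for scaling it to other regions is intended (Patient and public involvement). Both uses need harms information that can be read at face value. An empty or short harms list collected this way could mean few harms or few questions asked, and the reader could not tell which.

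**Working it through.** The document states no figure for harms, so there is none to reproduce. The group sizes come from Power analysis: 36 + 12 = 48, inflated for 20% drop-out to 36/(1 − 0.20) = 45 and 12/(1 − 0.20) = 15, total 60. These reproduce.

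**1. Is there another systematic source of harms?** Table 4 lists no adverse-event, fall or injury item. Three entries could reveal some events at follow-up: healthcare use (iMCQ), clinical characteristics (which include complications and comorbidities) and general questions. The harms text names none of them as a source. A fall or injury that led to no care need not appear in any of them.

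**2. What could a zero count have shown?** If all events are captured and none occurs in n people, the one-sided 95% upper bound on the risk is 1 − 0.05^(1/n).

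- n = 45: 1 − 0.05^(1/45) = 0.064, or 6.4%.
- n = 36: 1 − 0.05^(1/36) = 0.080, or 8.0%.

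If each affected participant is recorded only with probability c, the bound on the true risk becomes that figure divided by c. With c = 0.5 (assumed), it is 0.064/0.5 = 0.13 at n = 45 and 0.080/0.5 = 0.16 at n = 36. Under non-systematic reporting c is unknown, so no bound can be stated.

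**3. How much can incomplete capture hide?** The chance of recording at least one case is 1 − (1 − p·c)^n. Take a true risk of p = 5% (assumed):

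| n | c = 1 | c = 0.5 |
|---|---|---|
| 45 | 0.90 | 0.68 |
| 15 | 0.54 | 0.32 |

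**4. Could capture differ between the groups?** With equal true risks, the apparent risk ratio is simply the ratio of the capture shares (intervention/control). All shares here are assumed, because the document gives none:

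- 80% vs 50%: 1.6
- 60% vs 30%: 2.0
- 60% vs 80%: 0.75
- equal shares, however low: 1.0

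These values show only that the ratio can lie on either side of 1. They are not evidence of a difference. The text gives three reasons to think that capture might differ:

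- **Definition.** It ties harms to study participation. For controls, participation adds mainly measurements to usual care, so a fall during exercise is less likely to be labelled a harm.
- **Timing.** The groups are sequential (Implementation of ABI-MOTION intervention), so any change in researchers' vigilance over time coincides with group.
- **Contacts.** The intervention group has more contacts at which an event can surface.

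**The case against.** The strongest reply is that this is a disclosed and reasoned choice in a study that links existing services. Contraindications are examined and discussed, so the risk is not left unmanaged. Healthcare use, clinical characteristics and general questions are collected on the same schedule whatever the group. Focus groups, interviews and network meetings are analysed straight afterwards and used to adjust the intervention. The effect evaluation is declared exploratory, no statement of safety is promised, and the primary reach outcome, the sample size and the GEE models are untouched.

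Much of this stands, and it limits the point. It does not answer the under-counting. The safeguard cannot show whether it worked, the questionnaires are not assigned to harms, and qualitative meetings do not ask every participant about events.

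A reader might infer more: that harms will be counted unequally, with an excess in the intervention group because of the consultancy hours. The document does not support that. The consultancy is delivered by SportMEE's consultants, whereas harms are reported by the researchers, and nothing makes the consultants a reporting channel. The scheduled research contacts are not stated to differ by group, both groups have physician follow-up at about 6 and 12 months, and no between-group analysis of harms is planned. Unequal capture is a possibility, and its direction is open.

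The bounds also need care. They describe the whole intervention group. At the hypothesised 60% uptake of consultancy, 0.60 × 45 = 27 people would receive it, and zero events among them would give 1 − 0.05^(1/27) = 10.5%, even with full capture.

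**Conclusion.** The point holds as a worthwhile, inexpensive improvement. As written, the plan is likely to under-count harms, because collection is non-systematic, the definition filters on relatedness and no follow-up instrument is designated to detect events. Capture may also differ by group, but neither the size nor the direction can be derived from the document.

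What is lost is the ability to interpret a low count. Full capture would allow an upper bound of 6.4% (45 participants) or 8.0% (36 participants) after zero events; the planned method allows none. Those bounds follow from the planned group sizes. The 5% risk and all capture shares are assumptions used only for illustration.

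**What to change.** Add a short set of harms questions, identical in both groups, to the existing T1, T2 and T3 questionnaires, and ask them again at the T2 and T3 visits. They would cover falls, injuries, new cardiac or neurological events and hospital admission, each with date and activity. Asking at the visits matters because participants who cannot complete questionnaires independently, for example because of aphasia, are not required to do so (Data collection).

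Report all events by group regardless of judged relatedness, with relatedness shown separately, and give the number of people asked at each contact. State that harms will be described without a formal between-group comparison.

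The cost is slightly more participant burden and an amendment notified to the ethics committee. No visit is added and the sample size does not change. The study started on 1 March 2024, so participants already included would contribute only from their remaining contacts. Because controls were recruited first, they may have fewer of these left, which is a further reason to describe harms and not test them.
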